### Evaluation of study clinical and implementation outcomes

#### Clinical outcomes

The primary outcome will measure the proportion of patients with chronic HCV infection enrolled in the study that achieves SVR12 (cure) as defined by an undetectable viral load < 15 IU/mL at 12 weeks or later after treatment completion.

The secondary clinical outcomes measure is as follows:Time (in days) from being offered treatment to initiating treatment, among those enrolled in the studyProportion of patients enrolled in the study who initiate HCV treatmentProportion of patients enrolled in the study who complete HCV treatment

#### Implementation outcomes

The research team will measure key implementation outcomes to evaluate how the new site-specific HCV treatment workflows are utilized, integrated, and maintained in real-world organizational structures across our clinical sites. Key implementation outcomes include reach, effectiveness, adoption, implementation, and maintenance, as defined by the evidence-based RE-AIM framework [18]. Analyses of these outcomes will inform the potential for “real-world” scale-up of the HCV treatment intervention in the routine practice of other primary care clinical settings and across healthcare systems.

Strategies for measuring RE-AIM outcomes are shown in Table 3. Our primary and secondary clinical outcomes will measure effectiveness. We will use a combination of data collected from qualitative interviews and quantitative data from chart review to evaluate the implementation outcomes. Reach and effectiveness will be measured quantitatively using data extracted from the EMR and our REDCap database of patient-reported outcomes. Adoption will be measured quantitatively by extracting this data from REDCap. Additionally, we will conduct follow-up qualitative interviews with one or two clinical staff at each site to get a qualitative assessment of the implementation, maintenance, and acceptability of the adapted site-specific HCV treatment workflows to the clinic-specific teams. A convenience sample of 1–2 staff (provider and MA or nurse) from each site (7–14 total sample) will be used. Interviews will be audio-recorded and transcribed for analysis. For implementation, we will develop a rubric to measure fidelity to the site-specific HCV treatment workflows and will perform a fidelity assessment by chart review on a random sample of 10% of patients enrolled in the trial. The EMR will be reviewed for each patient to see how closely these workflows were implemented as intended, including examining the appropriateness, timing, and frequency of labs ordered.

**Table 3 Tab3:** RE-AIM measures

Implementation outcome	Measurement strategy	Data collection methodology
Reach	Reach of the site-specific HCV treatment workflows: the proportion of study participants who are offered HCV treatment *(Offered HCV treatment will be measured by the presence of a prescription for an HCV medication in the EMR)*	Primary data collection EMR chart review
Effectiveness	Primary outcome: the proportion of study participants that achieve SVR12 Secondary outcomes: the proportion of study participants that complete treatment. The proportion of study participants that initiate treatment	Primary data collection
Adoption	The proportion of providers who are trained per site	Primary data collection
Implementation	The extent to which the site-specific HCV treatment workflows are implemented as intended (fidelity) for study participants Markers include the following: the proportion of study participants who were genotyped, among study participants who reached SVR12. The proportion of study participants for whom an ultrasound was ordered, among non-cirrhotic study participants who reached SVR12	EMR chart review and qualitative interviews with clinic staff
Maintenance	The extent to which the site-specific HCV treatment workflows are sustained over the study’s 16-month data collection period	EMR chart review and qualitative interviews with clinic staff

### Sample size justification

We predict that we will achieve SVR12 in 75% of patients enrolled in our study. We will use the “intention-to-treat” principle by including those enrolled in the study and lost to follow-up in the denominator. Therefore, the denominator will consist of the population of patients at participating clinical sites who have been screened and diagnosed with chronic HCV infection and who have provided informed consent to participate in our study, regardless of whether treatment was initiated or not. These estimates were based on experience treating HCV in this patient population, as well as three published studies of HCV treatment interventions for people experiencing homelessness in the primary care setting [9, 10, 21].

With the expectation that 75% of patients enrolled in the study will achieve SVR12, a two-sided 95% confidence interval will be constructed with a half-width no more than 5% from the point estimate. In order to assure with 95% confidence that the true proportion achieving SVR12 under the locally contextualized site-specific HCV treatment workflows is within 5% of the observed proportion, the required sample size is 289 patients (Fig. 2).

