## Methods/design

### Setting

The study will be implemented at seven primary care clinics within CommUnityCare (CUC), Austin’s largest federally qualified health center (FQHC) network, which houses Austin’s Health Care for the Homeless program. The study sites were selected because of their focus on care for vulnerable, high-risk populations for HCV, including PEH and PWID. The study site locations include the following: (1) a full-spectrum primary care clinic located within the Austin Resource Center for the Homeless (ARCH) shelter (“the ARCH Clinic”); (2) a patient-centered medical home providing full-spectrum primary care for PEH as well as other medically complex and socially vulnerable patients following hospital discharge (“care connections”); (3) CUC’s dedicated clinic providing buprenorphine to individuals with opioid use disorder (medication-assisted therapy (MAT) clinic — “the MAT Clinic”); (4) a street medicine team brings care to PEH, meeting them at homeless campsites and under bridges (“the street team”); (5) a clinic located at Community First! Village (CFV), a permanent supportive housing community for individuals who were chronically homeless (“the CFV Clinic”); (6) a clinic located at Esperanza Community, a state-sanctioned encampment for PEH that is becoming a transformational shelter complex (“the Esperanza Clinic”); and (7) a full-spectrum primary care clinic space setup within Sunrise Church, providing care alongside the local mental health authority and other social service providers that partner with the Sunrise Homeless Navigation Center nonprofit that serves PEH in Austin (“Sunrise”).

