### Analytical approach

We will quantify the proportion of the study population with HCV that achieved SVR12, including a confidence interval for this proportion, using the “intention-to-treat” principle as detailed above. Secondary analyses will follow the “per-protocol” approach where the denominator will exclude participants lost to follow-up.

Participants who do not pick up all their HCV medication and who do not complete a final laboratory test for viral load by the end of the trial period will be recorded as not having completed treatment, considered lost to follow-up, and assumed to have not achieved SVR12. Participants who either miss or delay treatment doses or who do not pick up all treatment doses, but return for a treatment completion lab or SVR12, will be retained within the dataset and recorded as non-adherent for descriptive analyses. We will also evaluate the number and proportion of patients moving through each step of the HCV care cascade, from diagnosis of HCV and enrollment to achieving SVR12 in order to better understand barriers within the care cascade. General reasons for failure to initiate and complete treatment will be discussed with clinic staff and summarized, as will delays between each step of the care cascade.

To derive proportions and 95% confidence intervals (95% CI), we will apply generalized estimating equations (GEE) to logistic regression models without predictors and interpret the anti-logit of the intercept as our proportion. Bias-corrected GEE will be applied to account for a small sample size. We will examine characteristics of the patient population stratified by achievement of SVR12. These characteristics will include age, sex, race, ethnicity, housing factors, education, employment status, payor, mental health conditions and psychiatric diagnoses, substance use history, sexual behavior, medical comorbidities, clinical site, and adherence to HCV treatment. These characteristics will also be evaluated after adjusting for covariates using a multivariable logistic regression model. Reported outcomes will include adjusted odds ratios for SVR12 and their 95% confidence intervals. We will use GEE models to account for clustered data and correct for small sample size, as described above. We will also conduct similar exploratory analyses for our secondary outcomes.

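### The promised half-width of at most 5 points is sized for independent patients, whereas the planned interval allows for clustering and should be expected to be wider

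*Protocol article*

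**What the plan says.** The sample size rests on precision alone. In the Protocol article, Sample size justification, the expected result is given as "We predict that we will achieve SVR12 in 75% of patients enrolled in our study". The target is that "a two-sided 95% confidence interval will be constructed with a half-width no more than 5% from the point estimate", and from this "the required sample size is 289 patients". Non-completers cause no loss of numbers, because the denominator is defined by "including those enrolled in the study and lost to follow-up in the denominator". The section mentions no clustering, ICC or design effect.

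The Analytical approach section specifies how the proportion and its 95% interval will be obtained: a logistic GEE with an intercept only, back-transformed, with a bias correction for small samples. Later in the same paragraph it gives the reason: "We will use GEE models to account for clustered data and correct for small sample size, as described above". The Setting section says "The study will be implemented at seven primary care clinics", and the section on Objective 2 has each clinic adapt its own workflow.

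**The concern.** The sizing and the analysis use different variances for the same proportion. The sizing treats 289 patients as independent. The analysis lets patients in the same cluster be correlated, which normally widens the interval.

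Some variation between clinics is to be expected. They include a street team, a shelter clinic, a buprenorphine clinic and a supportive-housing clinic, and the workflows differ by design. Patients who never start treatment stay in the denominator, so clinic differences in access, initiation and retention all feed into the cure proportion.

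What is at stake is the stated precision. The trial has one arm and no hypothesis test behind its size, so the 5-point half-width is the only justification given for 289.

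**Working it through.** **Inputs from the Protocol article.** Expected proportion p = 0.75, two-sided 95% confidence, half-width d = 0.05, N = 289 (Sample size justification); 7 clinics (Setting).

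**Assumptions, not in the document.** ICC of 0.01, 0.02 or 0.05; clinic as the cluster; equal clinic sizes; and, as an alternative to the normal quantile 1.96, t on 7 − 1 = 6 degrees of freedom, 2.447. The article says that the GEE is bias-corrected but not which reference distribution goes with it.

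**Step 1. Reproduce 289.** n = z²p(1−p)/d² = 1.96² × 0.1875 / 0.0025 = 288.1, rounded up to 289. The half-width at 289 is 1.96 × √(0.1875/289) = 4.99 points. The figure showing the calculation is not in the text at hand, but an exact match to the independence formula leaves no room in it for a design effect.

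**Step 2. Find the reserve.** The bound fails once the design effect (DE) exceeds (5/4.992)² = 1.003. Mean clinic size is m = 289/7 = 41.3, and DE = 1 + (m − 1) × ICC, so the limit is an ICC of about 0.003/40.3, or roughly 0.0001.

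**Step 3. Expected half-width with clustering.** Half-width = q × √(DE × 0.1875/289), with q = 1.96 or 2.447. Between-clinic SD = √(ICC × 0.1875).

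| ICC (assumed) | Between-clinic SD, points | DE | Effective n (289/DE) | Half-width, normal | Half-width, t on 6 df |
|---|---|---|---|---|---|
| 0 | 0 | 1.00 | 289 | 4.99 | 6.2 |
| 0.01 | 4.3 | 1.40 | 206 | 5.9 | 7.4 |
| 0.02 | 6.1 | 1.81 | 160 | 6.7 | 8.4 |
| 0.05 | 9.7 | 3.01 | 96 | 8.7 | 10.8 |

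With the t reference the 5-point bound fails even at zero ICC.

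**Step 4. Sensitivity to unequal clinics.** With an assumed coefficient of variation of clinic size of 0.5, DE = 1 + ((1 + 0.5²) × 41.3 − 1) × ICC. The normal half-width becomes 6.1 points at ICC 0.01 and 9.4 at ICC 0.05.

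**Step 5. Would more patients restore 5 points?** With the number of clinics fixed at seven, N = (1 − ICC) / (d²/(z²p(1−p)) − ICC/7). With the normal reference and equal clinics this gives about 485 at ICC 0.01 and about 1,597 at ICC 0.02. Above an ICC of about 7/288.1 = 0.024 no number of patients suffices. Enlarging the trial is therefore not a practical remedy.

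**The case against.** Several objections have weight.

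- **The cluster unit is inferred.** The Analytical approach section never names it, and it lists clinical site among the characteristics to be examined against cure, so clustering by provider is not ruled out. This stands as a limit on the figures. Clinic remains the likelier reading, because 289 patients is not a small sample for a GEE whereas seven clusters is. Provider clusters would give a smaller design effect, but still a positive one if the ICC is positive.
- **The clustering sentence follows the multivariable model.** It may be read as applying only there. But it refers back to the earlier description, which is where the GEE and its correction are specified for the proportions.
- **The seven clinics could be regarded as fixed.** The aims concern patients at these clinics. On that view, differences between them do not undermine a binomial interval for their pooled proportion. But the plan chose a GEE for clustered data, and it is the GEE interval that has to be compared with the 5-point statement.
- **An article may leave detail to an analysis plan.** That covers the missing ICC and reference distribution. It does not cover a guaranteed half-width that the article states itself and that its own analysis does not support.

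A reader might infer that the reported interval will cover the true proportion less than 95% of the time. The documents do not support this. Under-coverage would affect a plain binomial interval when clinics are treated as random draws, and the plan does not report that interval.

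**Conclusion.** The stated precision is wrong for the planned analysis. The arithmetic behind 289 is correct; the independence assumption under it does not match the GEE interval. The 5-point bound holds only with an ICC of essentially zero and a normal reference.

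That there is no reserve does not depend on a chosen ICC; the size of the shortfall does. For an assumed ICC of 0.01 to 0.05, seven equal clinics and clinic as the cluster, the expected half-width is 5.9 to 8.7 points with a normal reference or 7.4 to 10.8 with t on 6 degrees of freedom. These are two separate ranges and should not be merged into one.

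The consequence is an interval wider than advertised. No decision threshold is tied to the 5 points, and the planned analysis already allows for clustering. This should be fixed, but it does not threaten the validity of the result.

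**What to change.** Keep 289 patients and the GEE analysis. In the Sample size justification section:

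1. State that ±5 points assumes independent patients, a true proportion of 75% and a normal reference.
2. Name the cluster unit.
3. Replace the 5-point guarantee with the half-width expected from the planned GEE at 289 patients, over a stated ICC range and with one declared reference distribution.

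The cost is a revised paragraph and no extra patients. The downside is that the stated precision becomes less favourable.

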**Fig. 2 Fig2:**
[figure not shown]
Sample size calculation

### Analytical approach

We will quantify the proportion of the study population with HCV that achieved SVR12, including a confidence interval for this proportion, using the “intention-to-treat” principle as detailed above. Secondary analyses will follow the “per-protocol” approach where the denominator will exclude participants lost to follow-up.

Participants who do not pick up all their HCV medication and who do not complete a final laboratory test for viral load by the end of the trial period will be recorded as not having completed treatment, considered lost to follow-up, and assumed to have not achieved SVR12. Participants who either miss or delay treatment doses or who do not pick up all treatment doses, but return for a treatment completion lab or SVR12, will be retained within the dataset and recorded as non-adherent for descriptive analyses. We will also evaluate the number and proportion of patients moving through each step of the HCV care cascade, from diagnosis of HCV and enrollment to achieving SVR12 in order to better understand barriers within the care cascade. General reasons for failure to initiate and complete treatment will be discussed with clinic staff and summarized, as will delays between each step of the care cascade.

To derive proportions and 95% confidence intervals (95% CI), we will apply generalized estimating equations (GEE) to logistic regression models without predictors and interpret the anti-logit of the intercept as our proportion. Bias-corrected GEE will be applied to account for a small sample size. We will examine characteristics of the patient population stratified by achievement of SVR12. These characteristics will include age, sex, race, ethnicity, housing factors, education, employment status, payor, mental health conditions and psychiatric diagnoses, substance use history, sexual behavior, medical comorbidities, clinical site, and adherence to HCV treatment. These characteristics will also be evaluated after adjusting for covariates using a multivariable logistic regression model. Reported outcomes will include adjusted odds ratios for SVR12 and their 95% confidence intervals. We will use GEE models to account for clustered data and correct for small sample size, as described above. We will also conduct similar exploratory analyses for our secondary outcomes.

Implementation outcomes will be analyzed descriptively. For the qualitative portion of the RE-AIM implementation outcomes, we will double code and analyze the audio-recorded and transcribed interviews using thematic descriptive and interpretive coding techniques. Secondary analysis will be done for some of the RE-AIM implementation outcomes. Secondary analysis for effectiveness may include percent of study participants who reached SVR12 that were non-adherent (missed or delayed doses). Secondary analysis for adoption may include two measures: (1) proportion of study participants initiating treatment of all offered, where the proxy for offered treatment is submitting a written prescription, and (2) proportion of study participants who pick up the first bottle of medication as a proxy for initiating treatment, therefore adopting the site-specific HCV treatment workflows. Secondary analysis for implementation will examine how fidelity affects the primary outcome in the aggregate.

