#### Objective 4: Prospective single-arm intervention trial

By designing and adapting HCV treatment workflows for each specific clinical site and training frontline healthcare providers, we hypothesize that we can effectively treat HCV across multiple primary care clinics serving vulnerable, high-risk populations. We plan to enroll 289 patients over 6 months. Following the baseline assessment, design of the site-specific HCV treatment workflows, and training of frontline healthcare providers, we will implement the workflows across our seven clinical sites and measure both clinical and implementation outcomes. The SPIRIT figure shows the timeline of enrollment, intervention, and assessments for the trial (Table 2). The SPIRIT checklist is provided in Additional file 1.

**Table 2 Tab2:** Erase Hep C study SPIRIT figure

	Screen	Enrollment	Treatment				
			Start	End (Glecaprevir / Pibrentasvir)	End (Sofosbuvir / Velpatasvir)	SVR12 (Glecaprevir / Pibrentasvir)	SVR12 (Sofosburvir / Velpatasvir)
Timepoint	***T***_**-1**_	***T***_**0**_	***T***_**1**_** = up to 90 days after *****T***_**0**_	***T***_**2**_** = *****T***_**1**_** + 60 days**	***T***_**3**_** = *****T***_**1**_** + 90 days**	***T***_**4**_** = *****T***_**2**_** + (90–120 days)**	***T***_**5**_** = *****T***_**3**_** + (90–120 days)**
ENROLLMENT:							
Eligibility Screen	X						
Informed Consent		X					
Interview		X		X	X		
Obtain EMR Data	X	X	X	X	X	X	X
INTERVENTION:							
Implement Site-Specific HCV Treatment Workflows		X	X	X	X	X	X
ASSESSMENTS:							
Demographic Variables		X		X	X		
Socioeconomic Variables		X		X	X		
Substance Use Variables		X		X	X		
Sexual Behavior Variables				X	X		
Medical History		X		X	X		
Labs	X	X		X	X		
SVR12						X	X
2º Clinical Outcomes			X	X	X	X	X
2º Implementation Outcomes			X	X	X	X	X

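### Clinical site is a predictor in a GEE whose natural clusters are the same sites, so the planned small-sample-corrected intervals for the site odds ratios are not valid

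*Protocol article*

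**What the plan says.** All of this is in the protocol article, section Analytical approach, unless noted.

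- For proportions, the plan is to "apply generalized estimating equations (GEE) to logistic regression models without predictors and interpret the anti-logit of the intercept as our proportion". The small-sample sentence, "Bias-corrected GEE will be applied to account for a small sample size", follows directly and belongs to these models, which contain no site term.
- The section then lists 14 patient characteristics to be compared by SVR12 status. The list ends with "sexual behavior, medical comorbidities, clinical site, and adherence to HCV treatment". The same characteristics are to be evaluated in a multivariable logistic model, and adjusted odds ratios with 95% confidence intervals will be reported.
- For that model: "We will use GEE models to account for clustered data and correct for small sample size, as described above". Similar exploratory analyses are planned for the secondary outcomes.
- Objective 4 gives the structure: "we will implement the workflows across our seven clinical sites and measure both clinical and implementation outcomes".

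The section names neither the cluster unit nor the variant of bias correction.

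**The concern.** Each patient contributes one SVR12 result, so the patient cannot be the cluster. Workflows are designed, adapted and delivered site by site. The reference to a small sample also fits seven clusters better than 289 patients. On that reading the adjusted model spends six parameters on site indicators and then estimates its variance from variation between those same sites. The indicators have already absorbed that variation, so the sandwich has almost nothing left from which to estimate the uncertainty of the site terms.

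At stake are the adjusted odds ratios by site for SVR12 and for the secondary outcomes. Depending on the software and the correction, their intervals would be far too narrow, or so wide and erratic that they say nothing, and there may be no warning.

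**Working it through.** **1. The plan's own figure.** Inputs from Sample size justification: expected SVR12 of 0.75, half-width 0.05, two-sided 95%. n = 1.96² × 0.75 × 0.25 / 0.05² = 288.1, rounded up to 289. The stated figure ("the required sample size is 289 patients") is reproduced. With seven sites, that is about 289 / 7 = 41 patients per site if sites are equal in size.

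**2. Singularity (algebra).** For site i let D_i = A_i X_i, where A_i is the diagonal matrix of μ(1−μ). Let V_i be the working covariance, M = Σ D_j′V_j⁻¹D_j, and H_i = D_i M⁻¹ D_i′V_i⁻¹.
- With site in the model there is a vector e_i such that X_i e_i = 1 and X_j e_i = 0 for every other site.
- Hence M e_i = D_i′V_i⁻¹A_i 1.
- Put u′ = 1′A_i V_i⁻¹. Then u′H_i = (1′A_i V_i⁻¹D_i) M⁻¹ D_i′V_i⁻¹ = e_i′D_i′V_i⁻¹ = u′.
- So u′(I − H_i) = 0, and I − H_i is singular for every site. Under working independence u is a vector of ones.

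This does not depend on site sizes, covariates or effects. Mancl-DeRouen needs the inverse of I − H_i and Kauermann-Carroll its inverse square root. Neither exists in standard form.

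**3. Numerical check.** Assumed settings: 7 near-equal sites (41-42 each), 289 patients, 1, 5 or 13 binary patient-level covariates, six site indicators, working independence, about 1,500 runs per setting. The smallest eigenvalue of I − H_i was about 1e-16 in every run. With site left out it was about 0.82 (1 covariate) or 0.68 (13 covariates), and the correction exists.

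Site terms, median standard error and coverage of the nominal 95% interval:

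| Variance | 1 covariate | 5 covariates | 13 covariates |
|---|---|---|---|
| Fay-Graubard | 0.020; 6.1% | 0.064; 18.6% | 0.117; 29.6% |
| Mancl-DeRouen, pseudo-inverse | 0.022; 7.3% | 0.071; 20.5% | 0.135; 32.5% |
| Morel-Bokossa-Neerchal | 0.413; 82.6% | 0.420; 83.0% | 0.447; 83.8% |
| Model-based | 0.583; 95.7% | 0.583; 95.9% | 0.605; 95.3% |

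The coverages fit the standard errors. If the model-based value is about right, coverage should be near 2Φ(1.96 × SE / model-based SE) − 1. For Fay-Graubard with 13 covariates, 1.96 × 0.1173 / 0.6054 = 0.380, which gives 29.6%.

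Forcing the standard Mancl-DeRouen inverse gave median site standard errors of 6.3, 12.1 and 38.1. Coverage was 93-94%, but these standard errors come from inverting a numerically singular matrix, and the intervals carry no information. In four test data sets, a standard bias-reduced GEE routine returned site standard errors from about 0.4 to over 87,000.

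**4. Patient-level covariates in the same model.** Fay-Graubard and pseudo-inverse versions covered 89-93% with 1.96, and about 95-97% with t on 6 df. Standard Mancl-DeRouen and Morel-Bokossa-Neerchal covered 91-97% with 1.96.

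**5. Rank.** The sandwich had rank at most 6, against 1 + 1 + 6 = 8 to 1 + 13 + 6 = 20 parameters. A joint Wald test of all terms cannot be formed.

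**6. Primary model.** The intercept-only model has no site term. Its bias-corrected standard error was well defined (0.09-0.18 on the logit scale in the four test data sets).

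**The case against.** **The cluster unit is not stated.** The Data collection section extracts the primary care physician, so provider is another possible unit, and an article may leave such detail to the analysis plan. This stands as a limit: clustering on site is an inference. It does not remove the point, because the article itself commits site to the adjusted model and GEE with correction to that same model.

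**The correction is not named, and some variants can be computed.** True. A reader might infer that no corrected variance exists at all, and that goes too far. But the computable variants do not rescue the site odds ratios with 1.96. Using 2.45 (t on 6 df) in the approximation of step 3 still gives only about 7% (1 covariate) to 36% (13 covariates) for Fay-Graubard. Morel-Bokossa-Neerchal would rise to roughly 92-93%, so that one combination would be tolerable. The article specifies neither element of it.

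**Sites would falsely look different.** A reader might infer this for every correction. It follows for those that shrink the site standard errors. Where software inverts the singular matrix numerically, the result is erratic and often plainly broken.

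**All reported intervals are wrong, or the primary interval is too narrow.** The documents support neither reading. Patient-level intervals are only mildly affected. The primary proportion comes from a model without predictors. The article states no multiplier or working correlation for it, and those are details for the analysis plan.

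**Importance.** None of the four objectives, the clinical outcomes or the RE-AIM measures is a comparison of SVR12 between sites. Site appears once in this analysis, as one of 14 characteristics. That confines the point to secondary and exploratory results.

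**Conclusion.** Wrong as written, within a narrow scope. If the seven clinics are the clusters, the stated adjusted analysis does not give valid 95% intervals for the site odds ratios. The standard leverage-inverse corrections are undefined. The computable ones cover about 6-33%, or 83-84% for Morel-Bokossa-Neerchal, against 95-96% for model-based standard errors. Joint tests of all terms are also lost. The same applies to the exploratory models for secondary outcomes if they have the same form.

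The singularity is exact and rests on two conditions only: clusters are sites, and site enters as indicators. The coverage figures also rest on assumed near-equal site sizes, binary covariates and working independence, so they show the order of magnitude and are not forecasts. The primary SVR12 proportion and the sample size of 289 are untouched.

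**What to change.** Name the cluster unit in the Analytical approach section. If it is the site, do not use site both ways. Choose one of these for each question:

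- **Site odds ratios:** ordinary or penalised logistic regression with site as a fixed effect, model-based standard errors and no site-level sandwich.
- **Patient-level odds ratios:** the bias-corrected GEE clustered on site, with site removed from the mean model and the correction named. In the simulations without site, Mancl-DeRouen covered 92.0% (1 covariate) and 93.5% (13 covariates) with 1.96, and 96.7% and 97.1% with t on 6 df.

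The cost is analysis wording only, with no change to design, data collection or sample size. The fixed-effects model spends six parameters on site and may need penalisation if some sites enrol few patients. The site-clustered GEE without site gives no site odds ratios, so these would have to come from the first model or from description.
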